### Overview of changes to the original statistical analysis plan for the primary and the secondary outcomes

Table 7 presents an overview of the changes relative to the original statistical analysis plan and explain the reasoning behind. The only substantial changes relative to the original plan includes that we now: (1) adjust the analyses by the protocol-specified stratification variable, i.e. nationality to improve the power [15]; (2) power calculations for secondary outcomes; (3) address the multiplicity problem by using a fixed-sequence procedure starting with the primary outcome followed by the secondary outcomes ordered according to falling power; (4) due to the low power involved in detecting small (1–5%) differences in mortality between the groups, assign worst possible score to patients who are not alive at the planned date of measurement of the continuous scores; (5) include auxiliary variables in the potential multiple imputation of missing value of the primary outcome to improve the efficiency of the imputation; and (6) outline a supplementary exploratory analysis of the temperature measurements and time to death; (7) substantial reduction of sample size.

**Table 7 Tab7:** Total number of serious adverse events (SAEs), and number of patients with at least one SAE groups in each analysis set (intention-to-treat or per protocol)

Types of events	Group 0			Group 1		
	Events, N	Patients with at least one event, N	Patients assessed, N	Events, N	Patients with at least one event, N	Patients assessed, N
Any event						
Event type 1						
Event type 2						
Event type 3						
Etc						

## Discussion

With this updated detailed statistical analysis plan we present the different analyses in the main publication of the EuroHYP-1 trial to avoid risks of outcome reporting bias and data driven results [16, 17]. Of the pre-specified outcomes in the trial, we choose to report only the primary outcome, the secondary outcome, two exploratory outcomes including serious adverse events in the main publication because of the complexity of the remaining safety variables and the detailed economical quantities that require separate publications.

### The interpretation of the effect on outcomes which may only be measured in surviving patients

Formally, three of the original secondary outcomes (NIHSS, EQ-5D-5 L, and infarct size) are only measurable in patients who survive until these outcomes were planned to be measured. This may make the interpretation of a significant effect on each of the last four secondary outcomes somewhat difficult when the power of detecting a small difference between the mortalities in the two groups is low. A surplus of patients in one intervention group relative to the other group may die before the outcome is measured. In the other intervention group, the corresponding surviving patients may (or may not) have very poor outcome values which may make the first group look good if the mortalities do not differ significantly.

Given the sample size of 800 patients and assuming the mortality in one group is 0.17 (e.g. in the control group, see above) the probability of not detecting an absolute reduction in mortality in the experimental group of 0.01, 0.02, 0.03, 0.04, and 0.05 is 0.93, 0.89, 0.81, 0.70, and 0.57, respectively. Thus, differences in mortality of the intervention groups of 5% or less are likely to remain undetected with a relatively high probability. Therefore, we have elected to include the dead patients in the comparison between the two intervention groups by assigning the worst possible score to the dead patients. The EQ5D5L is used to estimate QALYs gained in each arm of the trial population. QALYs are estimated by summing up the time spent in each state multiplied by the quality of life attributed to this state. By definition, the value of QALYs is zero from the time of death onwards. Total QALYs will be computed and reported for each patient for the entire duration of the follow-up.

For the study of prognostic markers in the EuroHYP-1 trial, we will apply similar principles as in the Clarithromycin in Patients with Stable Coronary Heart Disease trial (CLARICOR) trial [18]. The study of prognostic markers will not be part of the primary publication.

In conclusion, major adjustments compared with the original statistical analysis plan encompass: (1) adjustment of analyses by nationality; (2) power calculations for the secondary outcomes; (3) use of a fixed-sequence testing procedure starting with the primary outcome followed by the secondary outcomes ordered according to falling power to address the multiplicity problem; (4) assignment of worst possible score to patients who are not alive at the planned date of measurement of the continuous scores; (5) improved imputations; (6) outline of a supplementary exploratory analysis of the temperature measurements and time to death; and (7) substantial reduction of sample size.

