### Statistical analyses

#### Analytical principles

Analyses will be conducted according to the intention-to-treat principle [2] if not otherwise stated.

All primary tests of significance will be two-sided with alpha = 5%. Analyses will be conducted blinded with the two intervention groups coded as, e.g. 0 and 1. Two conclusions will be drawn, one assuming 0 is the intervention group and 1 is the control, and one assuming the opposite. After two abstracts with two conclusions have been written and both accepted by the Steering Group, the code will be broken.

The primary analyses of primary, secondary, and exploratory outcomes will be those of the intention-to-treat population adjusted for the protocol-specified stratification variable and the minimisation variables, and if necessary using data sets generated using multiple imputation.

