#### Power of the original secondary outcomes

As the sample size is based on the primary outcome, we have calculated the power of each of the originally planned secondary outcomes given the sample size of 800 patients.

Death day 91 ± 14 days after randomisation: the implied clinically relevant minimal change in mortality that needs to be detected may be calculated based on (1) the mortality of 17% found in the meta-analysis quoted in the protocol [1]; (2) the assumption that wherever the mRS is dichotomised, the odds ratio for treatment versus control will be the same, the ‘common odds ratio’; and (3) the requirement that this common odds ratio should not be larger than 0.74 (see the sample size calculation). Let the unknown change in mortality in the experimental group be x. If we assume the OR for the dichotomy mRS > 5 compared to mRS ≤ 5 will be 0.74 and the mortality of the control group is 17% as quoted in the meta-analysis, we may find x by solving the equation OR = ((0.17–x)/(0.83 + x))/(0.17/0.83) = 0.74 to obtain x = 0.0384 giving a mortality of 0.1700 – 0.0384 = 0.1316 in the cooled patients versus 0.1700 in the controls. Using a sample size of 800 participants, the power is found to be 0.33.

Death or dependency (mRS > 2) 91 ± 14 days after randomisation: using the same reasoning, the power of this outcome can be calculated by solving the equation (0.63–x)/(0.37 + x))/0.63/0.37 = (0.63 – x)0.63/(0.37 + x)0.37 = 0.74 as 63% of the patients in the meta-analysis had mRS > 2 implying x = 0.0725. The power may then be calculated to be 0.55.

NIHSS score 91 ± 14 days after randomisation: assuming a minimal relevant difference of 2 points, a standard deviation (SD) of 5 points [5], an α of 0.05, and a sample size of 800 participants, the power may then be calculated to 1.00.

EQ-5D-5 L score 91 ± 14 days after randomisation: assuming a minimal relevant difference of 0.05 points, a SD of 0.40 points [6–9], an α of 0.05, and a sample size of 800 participants, the power may then be calculated to 0.42.

WHODAS 2.0 score 91 ± 14 days after randomisation: we originally planned to analyse the World Health Organization Disability Assessment Schedule II (WHODAS 2.0) score at outcome assessment in the period day 91 ± 14 days after randomisation. However, due to difficulties in assessing the clinical meaning, we are not able to calculate the power, and we will thus analyse this as an exploratory outcome.

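### The five mortality miss probabilities fit 17% compared with a higher rate, not the stated reduction from 17%; they overstate the risk at 3 to 5 points and contradict the plan's own power of 0.33

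*SAP article*

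**What the plan says.** The Discussion section on outcomes measurable only in survivors sets its scenario as follows: "Given the sample size of 800 patients and assuming the mortality in one group is 0.17 (e.g. in the control group, see above"). For that scenario it states that the probability of missing "an absolute reduction in mortality in the experimental group of 0.01, 0.02, 0.03, 0.04, and 0.05 is 0.93, 0.89, 0.81, 0.70, and 0.57", in that order. It then concludes: "Thus, differences in mortality of the intervention groups of 5% or less are likely to remain undetected with a relatively high probability". The rule that the dead receive the worst possible score is presented as following from this.

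The same mortality comparison is treated earlier, under Power of the original secondary outcomes. There "the mortality of the control group is 17% as quoted in the meta-analysis", the common odds ratio of 0.74 implies a fall of 0.0384 to 0.1316, and the result is: "Using a sample size of 800 participants, the power is found to be 0.33". Table 2 repeats the 3.84% reduction and the power of 0.33.

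**The concern.** Two things look wrong.

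First, the two sections disagree. With baseline, sample size and alpha fixed, power must rise as the reduction grows. The power section gives 0.33 for a reduction of 0.0384, which is a miss probability of 0.67. The Discussion gives 0.70 for the larger reduction of 0.04, which is power 0.30. One method cannot produce both.

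Second, the series falls more slowly than it should for a reduction from 17%. A binomial variance shrinks as the rate moves down from 0.17 and grows as it moves up, so an increase is harder to detect than a decrease of the same size. The printed values look like those for an increase.

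What is at stake is limited but real. The figures are stated error rates in a published plan, and they are the quantitative reason given for a rule that the article lists among its major changes. They also tell the reader how likely a true mortality benefit is to go undetected, and death is a formally tested secondary outcome, last in the fixed sequence.

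**Working it through.** **Inputs**

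- Total sample size 800 (Discussion; Table 2). I take n = 400 per arm. Equal allocation is an assumption, because the article states no ratio; its 80:20 is the minimisation probability.
- Mortality p₁ = 0.17 in the control group (power section; Discussion).
- Reductions d = 0.01 to 0.05, so p₂ = 0.16, 0.15, 0.14, 0.13, 0.12 (Discussion).
- Two-sided alpha 0.05 (Analytical principles: "All primary tests of significance will be two-sided with alpha = 5"%), so z = 1.96.

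**Formula**

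Two-proportion z test without continuity correction. With p̄ = (p₁ + p₂)/2:

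- SE₀ = √[2p̄(1 − p̄)/n]
- SE₁ = √[(p₁(1 − p₁) + p₂(1 − p₂))/n]
- miss = Φ((1.96·SE₀ − |p₁ − p₂|)/SE₁) − Φ((−1.96·SE₀ − |p₁ − p₂|)/SE₁)

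**Step 1: reproduce the plan's own powers**

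| Outcome | Rates | Computed power | Stated |
|---|---|---|---|
| Death | 0.17 v 0.1316 | 0.329 | 0.33 |
| mRS > 2 | 0.63 v 0.5575 | 0.551 | 0.55 |
| At least one SAE | 0.20 v 0.10 | 0.978 | 0.98 |

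All three agree, so this is in effect the plan's method. With a continuity correction, death would have power 0.29, not 0.33.

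**Step 2: apply the same method to the Discussion series**

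Worked example for a 5-point reduction, 0.17 v 0.12: p̄ = 0.145, SE₀ = √(2 × 0.145 × 0.855/400) = 0.0249, SE₁ = √((0.1411 + 0.1056)/400) = 0.0248. The first argument is (1.96 × 0.0249 − 0.05)/0.0248 ≈ −0.048, and Φ(−0.048) ≈ 0.481. The second term is negligible. The miss probability is 0.48 and the power 0.52.

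For 0.17 v 0.22: SE₀ = 0.0280, SE₁ = 0.0280, the argument is about 0.176, and the miss probability is 0.57.

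| Difference | Printed | Reduction from 0.17 | Increase from 0.17 | Printed minus reduction |
|---|---|---|---|---|
| 0.01 | 0.93 | 0.933 | 0.934 | 0.00 |
| 0.02 | 0.89 | 0.880 | 0.886 | 0.01 |
| 0.03 | 0.81 | 0.784 | 0.806 | about 0.02 to 0.03 |
| 0.04 | 0.70 | 0.646 | 0.698 | 0.05 |
| 0.05 | 0.57 | 0.481 | 0.570 | 0.09 |

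The increase column rounds to all five printed values. The reduction column departs from them from 3 points onward.

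**Step 3: could another method rescue the printed series for a reduction?**

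| Variant, reduction from 0.17 | Miss at 0.05 |
|---|---|
| Unpooled or arcsine | 0.48 |
| Continuity correction | 0.52 |
| Fisher's exact test | 0.52 |
| 388 per arm (3% loss) | 0.49 |
| One-sided test | 0.36 |
| 33% to 50% of patients in control | 0.48 to 0.51 |

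None reaches 0.57. The continuity-corrected values come close at 1 to 4 points but fail at 5, and that correction does not reproduce the plan's 0.33.

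**Step 4: the internal contradiction**

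The power section gives a miss probability of 1 − 0.33 = 0.67 at d = 0.0384. The Discussion gives 0.70 at d = 0.04. The computed value at 0.04 is 0.65, which does lie below 0.67 as it must.

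**The case against.** The strongest defence is that the scenario sentence speaks of mortality in one group and names the control group only as an example. If 0.17 is instead the rate in the experimental group and control mortality is 0.18 to 0.22, the five figures are correct for a reduction. The fault would then lie in the label, not in the arithmetic. That is possible, and that the authors computed an increase is an inference from the five-for-five match. But the sentence names the control group and points back to the 17% control mortality of the power section, and under that reading the figures are wrong. Either way the text needs correcting.

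The second objection is that the concluding sentence has no direction. For a 5-point increase the miss probability is 0.57, and for a reduction 0.48 is still a high chance of missing the effect, well short of the trial's design power of 80%. This is fair. The general point about low power for mortality survives. What does not survive, for a reduction, is that a 5-point effect is more likely to be missed than found.

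Third, nothing operational rests on the series. The sample size, alpha, analysis models and test order do not use it, and the mortality power that feeds the test order, 0.33, is correct. The article also sets no decision rule for a neutral mortality result. All of this stands and limits the weight of the point, but it does not make the printed figures right.

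**Conclusion.** The point holds. For the stated scenario, a reduction from control mortality of 0.17 with 800 patients, the miss probabilities are 0.93, 0.88, 0.78, 0.65 and 0.48. The printed series is right at 1 point, nearly right at 2, and too high by about 0.02, 0.05 and 0.09 at 3, 4 and 5 points. At 5 points the implied power is 0.43 and the correct power about 0.52. The series also contradicts the plan's own power of 0.33 for a smaller reduction.

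This rests on a two-sided 5% test without continuity correction, which the plan's other powers confirm, and on equal allocation, which is assumed; other splits considered do not change the conclusion. The practical effect is modest: a 5-point reduction would still be missed nearly half the time, so the reason for scoring the dead as worst largely stands.

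**What to change.** In the Discussion, do one of the following:

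- replace the series with 0.93, 0.88, 0.78, 0.65 and 0.48 and keep the description as a reduction from a control rate of 0.17; or
- keep the printed series, state that it compares 0.17 with a higher rate of 0.18 to 0.22, and give the values for a reduction from 0.17 beside it.

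Then adjust the following sentence. Either confine the claim that an effect is likely to be missed to reductions of about 4 points or less, or say that a 5-point reduction has roughly even odds of detection. If both directions are shown, the sentence should say which one it refers to.

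The cost is a sentence or two of SAP wording. The worst-score rule, Table 2, the sample size and the test order need no change on account of this point.

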## Abbreviations

CHEERS: Consolidated health economic evaluation reporting standards
CLARICOR: Clarithromycin in Patients with Stable Coronary Heart Disease trial
DRG: Diagnosis-related group
EQ-5D-5 L: EuroQoL quality-of-life scale
EUDAMED: European Database on Medical Devices
EudraCT: European Clinical Trials Database
ITT: Intention-to-treat
MNAR: Missing not at random
mRS: Modified Rankin score
NIHSS: National Institutes of Health Stroke Score
OR: Odds ratio
QALY: Quality-adjusted life years
SAE: Serious adverse event
SAP: Statistical analysis plan
SD: Standard deviation
WHODAS: World Health Organization Disability Assessment Schedule
